## Data processing

The principal investigator will review and approve of the CRF pages for data entry. The data base for this study is created in Microsoft Access® software and shall be entered by two separate data entrants. The supervising data manager will do all the data reconciliations and validations leading to the validated file for each participant. The database is designed to keep track of all entries in time and password and will be able to provide a complete audit trail.

Any illegible CRF entries will be sent back to the clinical investigators with accompanying appropriate data query form. The monitor will also routinely check the database against the CRFs, and will ensure that all accumulated data query resolutions are verified as consistent on the database, CRF and source document.

Regular reports will be compiled for presenting to the DSMB for their ongoing review of safety data. This shall be in a blinded manner. The final analysis will be done immediately after day 84 to allow for phase IIb study Go/No go evaluation.

At the end of the study, all data queries will be resolved, data cleaned and accepted before database locking. After database lock, no further entry shall be possible, and this is set for month 14.

# Handling Biological samples

## Immunological samples

Before taking any samples, correct tubes and accessories shall be checked, and the tubes labelled accordingly. Blood shall be collected through the ante-cubital vein after appropriate antiseptic procedure as stipulated in the manual of SOPs into vacutainer tubes with anticoagulant. 4 to 5mL of blood will be taken when the antibody titration, WB and ADCI. An additional 10mL will be drawn for cell mediated immunity measurement.

Each plasma sample will be divided into 1mL cryotubes and kept at –70°C until antibody responses measurement. The fresh cells will directly used for ELISPOT and the remaining cryotubes at a rate of 18-20 million cells per tube in DMSO/FCS that shall be kept in a freezer at the temperature of –80°C for two days before they are transferred into a liquid nitrogen (to be kept at -170°C). Cryotubes must be correctly labelled with the volunteer’s identification code, the date of sample collection, the day of the visit and the cryotube’s number with indelible ink.

Aliquoting must be performed subject by subject to avoid mixing blood tubes. The following procedure must be followed:

1. After centrifugation, the person responsible for aliquoting should carry out the operation by taking the tubes one by one from the centrifuge.
2. The operator will place the cryotubes in a rack before aliquoting and will affix the completed labels onto the tubes.
3. Aliquoting will be performed according to the required volume 1mL, the number of tubes, and the priority of titrations.
4. Pre-labelled Nunc tubes that have not been filled for lack of serum will be removed.
5. The subject’s identification number and initials, the date of sampling, the number of aliquots obtained, and the date and time of aliquoting will be specified on the sample identification log. Labels will be affixed onto the three sheets of the list.
6. Comments may be made on the quality of samples (haemolysed, contaminated, etc.).
7. The next sample will be taken out of the centrifuge only when the steps 1 through 6 are completed.

## Storage Conditions

The analysis of cellular immunity will be done immediately on the freshly separated cells. The plasma aliquots have to be stored at -70°C for measurement of antibodies. The remaining separated mononuclear cells from the peripheral blood will be kept in liquid nitrogen for further controls or analyses.

Storage temperatures must be monitored and documented on the appropriate form as stipulated in the manual of procedures.

## Biological evaluation samples

Two separate tubes shall be used for haematology and clinical chemistry. One containing EDTA anticoagulant shall be used for the haemogram, and another plain tube for the urea.

These tests will be done in situ at the Vaccinology unit.

Table 1: Acceptable/normal ranges for blood testing

|  | Acceptable limit/ normal range | Toxicity grading scale | | | |
| --- | --- | --- | --- | --- | --- |
| Grade 1 | Grade 2 | Grade 3 | Grade 4 |
| Hemoglobin | ≥ 8.0 g/dL | < ULN | < 6.0 g/dL | < 5.0 g/dL | < 5.0 g/dL & clinical signs of heart failure |
| Total white cell count† | ≥ 4.0 x 103 /L  < 17 x 103 /L | 2.5 to 4.0 x 103 /L | 1.5 to 2.4 x 103 /L | 1.0 to 1.4 x 103 /L | < 1.0 x 103 /L |
| Platelets† | ≥ 100 x 103 /L | 50 to 99 x 103 /L | 25 to 49 x 103 /L | < 25 x 103 /L | < 25 x 103 /L & clinical signs of bleeding |
| ALT* | ≤ 60 mol/L | 1.1 to 2.5 x ULN | 2.6 to 5.0 x ULN | 5.1 to 10.0 x ULN | > 10.0 x ULN |
| Creatinine* | ≤ 60 mol/L | 1.1 to 1.5 x ULN | 1.6 to 3.0 x ULN | 3.1 to 6.0 x ULN | > 6.0 ULN or requires dialysis |
| † Grading scale adapted from Division of AIDS table for grading severity of adult and pediatric adverse events December 2004  * Grading scale adapted from WHO Toxicity Grading Scale for Determining Severity of Adverse Events, February 2003.  ULN: Upper Limit of Normal | | | | | |

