### Safety monitoring reports

In each group after all the subjects have completed the 7 days of follow up, a safety report will be produced for the DSMB. In total, 5 safety reports will be provided to the DSMB. An independent statistician will analyze the data and prepare an unblinded report for the DSMB thereby maintaining the blind of the study staff. If a criterion for the suspension of progression of the study is met, or the DSMB have any safety concerns about the vaccines, they may suspend the progression to the next sequential vaccine dose or to the next dose level. The process outlined in Sections 5.2.11 will be followed.

The reports will contain for each group:

- All SAEs and any relationship to vaccine;
- In each group, for each of the first two doses (i.e. after Dose 1 and Dose 2) of MSP3 and Hepatitis B, all solicited AEs tabulated by severity grading (any and Grade 3 alone) and relationship to vaccine;
- In each group, for each of the first two doses (i.e. after Dose 1 and Dose 2) of MSP3 and Hepatitis B, all unsolicited AEs tabulated by severity grading (any and Grade 3 alone) and relationship to vaccine;
- All laboratory values up to 28 days post Dose 2 presented as number of subjects out of range (above and below normal range) at each sampling time point (post doses 1 and 2 of MSP3 and Hepatitis B) tabulated by toxicity grading scale;
- All withdrawals of study subjects by the Principal Investigator due to adverse events recorded from the children or withdrawals of children by the parent(s)/guardian(s) following doses of MSP3 and Hepatitis B (expressed as percentage of subjects enrolled).

To allow the decision making for the progression to the next cohort, a comprehensive cumulative safety report of all the data collected up to date will be submitted to the DSMB in the same format as described above.

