## Exclusion criteria for enrolment

Any one of the following criteria will be exclusionary for this study:

1. Symptoms, physical signs of disease that could interfere with the interpretation of the trial results or compromising the health of the subjects.
2. Immunosuppressive therapy (steroids, immune modulators or immune suppressors) within 3 months prior recruitment. (for corticosteroids, this means prednisolone or equivalent  0.5 mg/kg/day. Inhaled and topical steroids are allowed).
3. Cannot be followed for any social, psychological or geographical reasons.
4. Use of any investigational drug or vaccine other than the study vaccine within 30 days preceding the first dose of study vaccine, or planned use up to 30 days after the third dose.
5. Suspected or known hypersensitivity to any of the vaccine components or to previous vaccine.
6. Laboratory abnormalities on screened blood samples out of range, more specifically refer to table 2.
7. Planned administration of a vaccine not foreseen by the study protocol within 30 days before the first dose of vaccine. An exception is the receipt of an EPI or licensed vaccine (measles, oral polio, meningococcal and combined diphtheria/pertussis/tetanus vaccines) which may be given 14 days or more before or after vaccination.
8. Evidence of chronic or active hepatitis B infection.
9. Presence of chronic illness that, in the judgement of the investigator, would interfere with the study outcomes or pose a threat to the participant’s health.
10. Administration of immunoglobulin and/or any blood products within the three months preceding the first dose of study vaccine or planned administration during the study period.
11. History of surgical splenectomy.
12. Moderate or severe malnutrition at screening defined as weight for age Z-score less than ‑2

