## Prior and Concomitant Therapy

Immunosuppressive or immune-modulator treatments are non-inclusion criteria. If it happens to be necessary to use one of them during the trial period, the data for the concerned participant will be considered as a deviation to the protocol.

Antipyretics or painkillers will not be allowed as preventive treatment of pain or fever, before vaccination. Concomitant vaccinations are not allowed during the study; an exception is the receipt of an EPI or licensed vaccine (measles, oral polio, meningococcal and combined diphtheria/pertussis/tetanus vaccines) which may be given 14 days or more before or after vaccination.

For all other treatments, the trade name of the drug, total daily dose, indication, start and stop dates will be required for the CRF completion (and, if appropriate, timing requirements within the day: AM, PM, post-vaccination shot)

Table 2 Summary of time periods between which different classes of concomitant medication/treatment/vaccination must be recorded

| **3 months prior to Dose 1  Dose 1** | All treatments listed as elimination criteria in Section 8.48.4 |
| --- | --- |
| **Screening  30 Days post Dose 3** | All antipyretic, analgesic, antibiotic and any treatments listed as elimination criteria in Section 8.4  All vaccinations |
| **31 Days post Dose 3  Final Study Visit** | All treatments listed as elimination criteria in Section 8.4 |
|  | |

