# Primary evaluation criteria

## Definition of the Criterion

The reactogenicity and the safety shall be assessed on the following criteria:

1. Immediate reactogenicity (within 60 minutes, with emphasis on allergic reactions),
2. Local and systemic reactogenicity during the 7 days following each vaccination.
3. Any unsolicited adverse events (AE) occurring outside scheduled visit times, up to one month after the third vaccine dose and requiring a physician visit
4. Any serious adverse events (SAE) whenever they occur during the trial period (from first visit to last visit). The relationship with the vaccine must be determined by the investigator, using the following definitions: **not related, possibly related, probably related, definitely related.**
5. Biological safety, assessed four weeks after each injection, in relation to the baseline data profile on the following:

RBC, haemoglobin, haematocrit, platelets, WBC, Liver enzymes (SGOT, GPT, total bilirubin) and creatinine.

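### Table 1 makes the same haemoglobin values both acceptable and Grade 1, and laboratory exclusion criterion 6 cites the wrong table

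*Protocol*

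**What the plan says.** Section 7.3 of the protocol holds "Table 1: Acceptable/normal ranges for blood testing". Its haemoglobin row is "Hemoglobin | ≥ 8.0 g/dL | < ULN | < 6.0 g/dL | < 5.0 g/dL": first the acceptable limit, then Grades 1, 2 and 3. The footnote reads "ULN: Upper Limit of Normal". The row gives no upper limit for haemoglobin, and it is the only row without a symbol pointing to a source grading scale.

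The grades have a stated use. Section 5.2.10 (Safety monitoring reports) requires laboratory values after Doses 1 and 2 to be "presented as number of subjects out of range (above and below normal range) at each sampling time point", broken down by the toxicity grades. Section 14.1 lists as an evaluation criterion "Biological safety, assessed four weeks after each injection, in relation to the baseline data profile", and haemoglobin is among the parameters named there.

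Exclusion criterion 6 in section 8.3 reads "Laboratory abnormalities on screened blood samples out of range, more specifically refer to table 2". Item 6 of the synopsis non-inclusion criteria says the same. The only table with that number, in section 11, is headed "Table 2 Summary of time periods between which different classes of concomitant medication/treatment/vaccination must be recorded".

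**The concern.** A toxicity grade is meant to mark a departure from the acceptable range. Here Grade 1 begins at the upper end of normal for a parameter whose only stated limit is a lower one. A child can be in range by one column and Grade 1 by the next. The text does not let a reader repair this safely. If the entry is a slip for a lower limit, nothing says whether that means the row's 8.0 g/dL or a laboratory reference limit, and two people could grade 8.5 g/dL differently.

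At stake is the haemoglobin part of the graded tables that the DSMB uses when reviewing progression to the next dose or dose level. The wrong table number matters because criterion 6 is the rule that turns screening blood results into eligibility. Meeting all eligibility criteria is also a condition of the according-to-protocol safety cohort (section 16.3.1.2).

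**Working it through.** The plan states no figure that can be reproduced here. The check compares entries, with one small calculation of size.

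**1. The haemoglobin row, taken literally and giving each value the highest grade it meets**

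| Haemoglobin (g/dL) | Acceptable-limit column | Grade |
| --- | --- | --- |
| 8.0 up to the ULN | in range | 1 |
| 6.0 to 7.9 | out of range | 1 |
| 5.0 to 5.9 | out of range | 2 |
| below 5.0 | out of range | 3 or 4 |

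The first line is the contradiction. The first two lines together show that Grade 1 does not separate acceptable from unacceptable values.

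**2. Comparison with another parameter where low values are the concern.** The platelet row runs "≥ 100 x 103 /L | 50 to 99 x 103 /L", so Grade 1 starts just below the acceptable limit. The white-cell row follows the same pattern, with acceptable values from 4.0 and Grade 1 from 2.5 to 4.0 (only the boundary value is shared). Haemoglobin departs from the table's own convention.

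**3. Number of children affected at baseline.** The protocol gives no ULN, so I take it as an upper percentile *q* of a healthy reference group and assume that the participants resemble that group. Expected number below the ULN = 45 × *q*:

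- *q* = 0.95: 45 × 0.95 = 42.75, about 43
- *q* = 0.975: 45 × 0.975 = 43.9, about 44
- *q* = 0.99: 45 × 0.99 = 44.55, about 45

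Per group of 15 the same calculation gives 14.25 to 14.85, so 14 or 15 children in each. As a stress test, suppose mean 11.5, SD 1.5 and a ULN of 12.5 g/dL (all assumed). Then 74.8% lie below the ULN, or 0.748 × 45 = about 34 children. Most children are Grade 1 even then.

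**4. Number of tabulated values affected.** The DSMB laboratory tables run to 28 days after Dose 2. Of the evaluation days in section 5.2.4, the post-dose ones in that span are D6, D28, D36 and D56: 4 × 45 = 180 values at most.

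**5. What a fall would look like.** Take a child who goes from 11.0 to 6.1 g/dL, with a ULN above 11.0. The grade is 1 before and 1 after, so the grade table shows no change. The acceptable-limit column moves from in range to out of range, so the out-of-range count does record the fall.

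**6. The cross-reference.** Criterion 6 cites Table 2. Table 2 holds recording periods and no laboratory value. The ranges are in Table 1.

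**The case against.** The strongest reply is that little depends on Grade 1 haemoglobin, and most of that reply stands.

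- A reader might infer that the safety tables cannot separate the arms or show a real fall. The documents do not support this. Section 5.2.10 also requires out-of-range counts, which use the 8.0 g/dL limit. Grades 2 to 4 do not refer to the ULN. Section 16.4 summarises continuous variables by group with medians, quartiles and ranges.
- A reader might infer that nearly every child would be recorded with an adverse event. Section 13.2 makes a laboratory finding an adverse event only when the investigator judges it clinically significant.
- No suspension criterion in section 5.2.11 uses a laboratory grade. Mandatory follow-up of laboratory results (section 13.4.2.4) concerns Grades 3 and 4 and clinically significant findings. Biological safety is an item in section 14.1 but is absent from the synopsis list of primary endpoints.
- A reader might count all nine evaluation days, 9 × 45 = 405 values. That exceeds the scope of the DSMB tables.
- A reader might say that screening has no usable laboratory reference. Table 1 is clearly captioned and is the only table of ranges, so the reference is wrong rather than unusable.
- Two other features of Table 1 might be read as errors. ALT shares its limit of 60 and a molar unit with creatinine. The unit deserves a check because ALT is an enzyme activity, but nothing in the document shows the limit to be wrong. White cells have an upper acceptable limit and no high-side grade; that can be a design choice, since values above range are counted anyway.

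None of this removes the contradiction in the haemoglobin row or the wrong table number.

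**Conclusion.** Both points hold as internal inconsistencies; no stated figure is miscalculated. Followed literally, the haemoglobin row puts about 43 to 45 of 45 children in Grade 1 at baseline, which makes that column of the DSMB tables uninformative for up to 180 post-dose values. The share rests on an assumed ULN at the 95th to 99th percentile and on participants resembling the reference group. The contradiction itself rests on no assumption. The effect is confined to the Grade 1 haemoglobin column, and the cross-reference error is clerical. This is worth correcting before the table is used, but it is not a flaw that puts the safety assessment as a whole at risk.

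**What to change.** - The sponsor should reconcile the haemoglobin Grade 1 entry with the row's acceptable limit and its Grade 2 threshold, so that no haemoglobin value is both acceptable and graded. Which thresholds are right is for the sponsor to decide; none is proposed here.
- Check the molar unit printed for ALT in the same table.
- In exclusion criterion 6, change the reference from Table 2 to Table 1, in section 8.3 and in the synopsis.

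The cost is one corrected table and two corrected cross-references. Visits, samples and sample size do not change. It should be done before screening starts, so that eligibility and grading use one settled table.

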# Trial participants

## Recruitment of participants

Following authorizations from the national ethics committee, the study information will be passed on to the community of Balonghin. Starting with the local village leadership, opinion holders and other gate keepers, meetings to introduce the study programme will be organised. There will be continuous exchange of information with the community with specific question and answer sessions at the community level. Once acceptability is ascertained, parents and guardians of children aged 1-2 years will be invited to participate in the study. Adequate time will be allowed for considering the study information and those willing to participate will be invited to consent for the screening.

At screening, full medical history and physical examination will be conducted by the study clinicians.

## Inclusion criteria for enrolment

Only participants who fulfil **ALL** of the following will be enrolled in the study and allocated a study ID number.

1. Children aged 1-2 years old
2. Healthy by medical history and physical examination
3. Signed /thumb printed informed Consent by guardian/parent
4. Resident in the study area village during the whole trial period

## Exclusion criteria for enrolment

Any one of the following criteria will be exclusionary for this study:

1. Symptoms, physical signs of disease that could interfere with the interpretation of the trial results or compromising the health of the subjects.
2. Immunosuppressive therapy (steroids, immune modulators or immune suppressors) within 3 months prior recruitment. (for corticosteroids, this means prednisolone or equivalent  0.5 mg/kg/day. Inhaled and topical steroids are allowed).
3. Cannot be followed for any social, psychological or geographical reasons.
4. Use of any investigational drug or vaccine other than the study vaccine within 30 days preceding the first dose of study vaccine, or planned use up to 30 days after the third dose.
5. Suspected or known hypersensitivity to any of the vaccine components or to previous vaccine.
6. Laboratory abnormalities on screened blood samples out of range, more specifically refer to table 2.
7. Planned administration of a vaccine not foreseen by the study protocol within 30 days before the first dose of vaccine. An exception is the receipt of an EPI or licensed vaccine (measles, oral polio, meningococcal and combined diphtheria/pertussis/tetanus vaccines) which may be given 14 days or more before or after vaccination.
8. Evidence of chronic or active hepatitis B infection.
9. Presence of chronic illness that, in the judgement of the investigator, would interfere with the study outcomes or pose a threat to the participant’s health.
10. Administration of immunoglobulin and/or any blood products within the three months preceding the first dose of study vaccine or planned administration during the study period.
11. History of surgical splenectomy.
12. Moderate or severe malnutrition at screening defined as weight for age Z-score less than ‑2

## Elimination criteria during the study

The following criteria should be checked at each visit subsequent to the first visit. If any become applicable during the study, it will not require withdrawal of the subject from the study but may determine a subject’s evaluability in the according-to-protocol (ATP) analysis.

- Administration of a vaccine not foreseen by the study protocol during the period starting from 30 days before Dose 1 and ending 30 days after Dose 3.
- Use of any investigational or non-registered product (drug or vaccine) other than the study vaccines during the study period.
- Administration of immunoglobulins and/or any blood products during the study period.
- Chronic administration (defined as more than 14 days) of immunosuppressants or other immune-modifying drugs during the study period (for corticosteroids, this will mean prednisone, or equivalent,  0.5 mg/kg/day. Inhaled and topical steroids are allowed).

## Contraindications to subsequent vaccination

### Indications for deferral of vaccination

The following AEs constitute contraindications to administration of MSP3 or Hepatitis B vaccines at that point in time; if any one of these AEs occurs at the time scheduled for vaccination, the subject may be vaccinated at a later date, within the time window specified in the protocol, or withdrawn at the discretion of the investigator. AEs should be followed-up accordingly:

- Acute disease at the time of administration of investigational product (acute disease is defined as the presence of a moderate or severe illness with or without fever). All vaccines can be administered to persons with a minor illness such as diarrhea or mild upper respiratory infection without fever, i.e. axillary temperature < 37.5°C.
- Axillary temperature of  37.5°C.

